#### b) Entomological

Previous studies with experimental huts indicated that DDT IRS deterred 60-70% of mosquitoes from entering houses [28]. LLINs were not associated with a deterrent effect in Gambian houses [15]. Based on a study using light traps in an adjacent study area in 2005, we expect that the mean number of female *An. gambiae s.l. *per trap will be 4.8 (with a coefficient of variation, k = 0.44). In order to demonstrate a 60% reduction in hungry indoor mosquitoes (i.e. unfed *An. gambiae*) associated with DDT IRS, with 90% power and at the 5% level of significance, we would require 8 houses in each cluster and 12 clusters in each arm of the trial over 2 years [27]. Since the number of mosquitoes rise and fall during the rainy season we propose to sample from each house 6 times each year. To allow for loss to follow-up due to people moving house during the study period we propose to include at least 8 houses in each cluster and 15 clusters in each study arm for 2 years.

### Data handling and record keeping

The demographic data will be recorded by fieldworkers and the clinical data by study nurses on standardised data forms. Each participant will have a unique identification (ID) number. All data recorded on individuals will be made by recording the anonymous ID.

Data forms will be scanned to produce electronic copies and into the data set using Snap Survey (Version 10, Snap Survey Ltd., Haymarket, London, UK) software and verified against electronic copies of the original forms by data entry clerks to produce 2 independently verified versions. These will be combined and errors corrected to produce a single dataset. This will be submitted to consistency checking by generic and study specific algorithms designed to identify sources of error. When inconsistencies are found, these will be checked against the original forms and subsequently amended in the dataset. Errors will be corrected when possible, with checking in the field when necessary and possible, to produce final datasets.

All forms with subject names and/or clinical data will be kept in a locked cabinet, when not in use, and the key kept by the study coordinator or delegate. These datasets will be, password protected. Data will be stored for at least 10 years. The clinical data will be kept separately from that containing personal information. All forms and datasets, apart from those for enumeration, will identify subjects by their subject specific ID and names will not be collected or entered. After the collection and verification in Snap Survey data will be moved to MRC's SQL server 2008 SWIFT. These datasets will be, password protected and only accessed by senior study staff and the study Data Manager. Data will be stored for at least 10 years.

The Principal Investigator (PI) will maintain appropriate medical and research records for this study in compliance with GCP and regulatory and institutional requirements. Authorised representatives of the sponsor, the ethics committee(s) or regulatory bodies may inspect all documents and records required to be maintained by the investigator. The PI or designee will ensure the access to facilities and the records.

The PI or designee will document and explain any deviation from the approved protocol on the CRF, where appropriate, and record and explain any deviation in a file note that will be maintained as an essential document. Deviations from the protocol, GCP or study specific requirements that might have an impact on the conduct of the study or the safety of participants will be reported within 15 working days to the sponsor and relevant Ethics Committee, as appropriate. Any other protocol deviation will be reported to the local EC together with the annual report.

### Analytical plan

#### Outcome 1 - malaria morbidity

The primary endpoint is a comparison of the incidence of clinical episodes of malaria in children in the 2 intervention groups, measured by PCD. After a case of malaria is treated, time of observation will be censored for 3 weeks and further attacks of malaria during this period are not considered. History of travel away from the village for prolonged periods will be captured by monthly surveys and time at risk will be censored for such periods. In addition, malaria cases in children who resided outside their study village for more than half the elapsed study period at the time of illness will be censored. An initial unadjusted analysis will be based on comparisons of the incidence rates between the 2 groups. Incidence rates will be calculated for each cluster and the ratio of their un-weighted means will give an estimate of the intervention effects. Confidence intervals for the intervention effect will be obtained using the approximations given by Bennett [29] and tested using a bootstrapped [30] confidence interval. The incidence rates for each cluster will also be used to perform a hypothesis test based analysis between the 2 groups using a 2 sample unpaired t-test. It is likely that the rates will be highly skewed and if necessary the rates will be transformed. Using the incidence rates as a response, linear regression can be used to adjust for cluster level covariate effects. If the assumptions of normality and constant variance cannot be met, a non-parametric test (Mann-Whitney) will be used to compare the 2 groups. The cluster randomised trial will result in a multi-level model with individuals within village. Individual level covariates will be modelled using random effects Poisson regression which will be fitted using GLLAMM, a Stata program to fit generalized linear latent and mixed models GLLAMM [31], to allow for the clustering effect of village, compound and the effect of repeated episodes in the same child. Year will be included as a fixed effect which will allow any interaction with the intervention to be quantified. Other potential confounders such as house architecture, bednet use and recent antimalarial treatment will also be adjusted for in the analysis. Should the data, be zero-inflated or under/over dispersed modifications to the underlying distributional assumptions will be examined. The time to first infection will be examined using a survival analysis approach. Initial unadjusted analysis will use Kaplan Meier curves to compare the probability of subjects in the two arms becoming infected as the malaria season progresses. A Cox regression frailty model will be used to adjust for covariates, allowing for the clustering. The location of the infected subjects will be known to the household level and this information will be used to examine the spatial distribution of infection over time. Within the larger villages formal methods such as k-means fuzzy clustering [32] will be used to quantify clusters of infection.

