## Methods/Design

### Study area and participant eligibility

The study is situated in the far east of The Gambia, in URR, extending approximately 240 to 320 km inland from the mouth of the Gambia River on the Atlantic coast, an area of open Sudan savanna. The climate consists of a single rainy season from May to October followed by a long dry season. This defines the highly seasonal malaria transmission with most malaria episodes experienced during or immediately following the rainy season. This region covers an area of 1995 km^2 ^and is bisected by the river into the north and south banks. The population of the region was 182,586 in 2003, the most recent census, with the majority living in small rural villages in houses made with mud or cement walls and thatched or metal roofs. The study's field station is based at Basse Santa Su town (UTM coordinates 13.3167N, -14.2167W) which is the only sizeable urban area.

Villages or groups of neighbouring villages, will be selected for the study that have > 110 children aged 6 months -13 years and that are ≥2 km from another study village to reduce likelihood of movement of mosquitoes from one cluster to the next. The study cohort of children, aged 6 months - 13 years old in June in Year 1, who are village residents, will be enumerated and an average of 110/cluster will be selected randomly and invited to participate in the clinical surveys and passive case detection (PCD). In order for the results from this study to be as generalizable as possible, no distinctions will be made regarding gender, ethnic group, medical condition or physical health. Children will be included providing their carers/parents give witnessed informed written consent and, in the case of older children, assent is provided. Assurance will also be sought from carers/parents that they expect that the child will remain resident in their village during the transmission season and will not be sent away for example for live stock herding or schooling. Subjects and households are free to withdraw from participating in the study at any time without giving a reason. If consent is not provided then replacement children will be randomly selected from those remaining. In year 2, overage children will leave the study and infants aged 6 to 18 months will be recruited; any other children who have left the study, for whatever reason, will be replaced.

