### Study procedures and evaluations

In advance of the spray campaign in year 1, spray operatives and supervisors will be trained on the WHO methods for IRS with DDT for two weeks by the NMCP vector control officer seconded to the project and an internationally recognized IRS consultant. They will be equipped with personnel protective clothing, including boots, long-sleeved cotton overalls, hat, gloves, mask and boots and trained in the maintenance and use of these. Spray operatives will use spray pressurized canisters made to WHO specifications WHO/VBC/89.970 (Hudson X-Pert^® ^Sprayer, 15L model 67422AD with stainless steel nozzle (8002E), flat fan pattern, 80° angle, flow rate 0.76L/min at 45psi pressure). They will be rigorously trained in the use of these and their maintenance. A 2-day refresher training will be provided before the spray campaign in year 2. Any remnant in the sprayers at the end of daily spraying will be collected following the "Progressive Rinse" method and recycled to minimize waste (http://www.hdhudson.com/global-public-health/newsletters/technical-information accessed 9th June 2011).

It is intended that both IRS and LLIN distribution will be completed in May both years. In year 2 all households in the arm randomized to this intervention will receive IRS as in year 1. LLIN distribution in year 2 will be to residents who have relocated to study villages since year 1.

Village health workers will be provided with refresher training on diagnosis of malaria, the use of RDT and study procedures in July 2010 by the study physician in collaboration with study nurses and the community health nurses. The methods used will be informed by ongoing studies in The Gambia on the introduction of RDT at all levels of health service. Refresher training will be provided in 2011 before the transmission season.

Movement of children will be assessed at monthly intervals on brief questionnaires to estimate the time at risk and bednet usage will be assessed during these house visits in August each year.

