### Sample Size Rationale

#### a) Clinical

Both LLINs and IRS alone reduce malaria morbidity by approximately 50% [5,6]. The combined impact of these two interventions is unknown. If the effects were simply additive a mean reduction of 75% could be anticipated for the combination, but the effects may be synergistic (e.g. by having a mass killing effect) or antagonistic (e.g. the repellency of DDT reducing *Anopheline *house entry and contact with LLINs). To cover these possibilities we expect that LLINs will reduce incidence by 50%, with LLINs and IRS combined reducing the residual incidence by 30-60% (i.e. 50% vs 65-80% fewer clinical cases of malaria). A study of 3-60 month old children during the end of the rainy season (Sept-Dec) in the URR in 2007 found a seasonal incidence of 0.79 (95% CI: 0.58-1.08) cases/child-years by PCD ([name] pers. comm.); ITN prevalence was 50%. We estimate conservatively that increasing LLIN provision to > 80% and inclusion of older children will reduce incidence rates by about 60-80%, so incidence rates of 0.30 (LLINs) to 0.15 cases/child-years (LLINs & IRS) have been included in the sample size estimations. The study will also record PCD over two high transmission seasons, not 1 as in the [name] study, further enhancing our ability to detect differences between study arms. Estimations for k, the corrected coefficient of variation to adjust for between cluster variation (based on within and between cluster variation) [27], from a cluster trial conducted in the Central River Region of The Gambia in 2006/7 ([name] personal communication) varied from 0.31-0.43 and has been used to explore sample sizes (Figure 2). Two of the 5 districts in URR have 70 villages suitable for the trial with over 100 children aged 6 months-14 years (predicted from the 2003 National Census) and could accommodate an average cluster size of 110 children (range 75-125). We plan to follow these children for 22 weeks covering the peak malaria incidence season each year, which, allowing for a 20% drop out rate over the 2 years, yields 74.4 child-years per cluster. The graphs below indicate a sample size of 5-39 clusters per arm (Figure 2). Since estimates for incidence and drop-out rate are conservative and the value of k may also be reduced by the stratified design, we will recruit 35 clusters in each arm of the trial.

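### The residence exclusion for the primary endpoint removes malaria cases but states no matching removal of resident person-time in equally mobile children without malaria

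*Protocol article*

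**What the plan says.** All of this is in the Protocol article. Under Analytical plan, Outcome 1 - malaria morbidity, two residence rules follow one another.

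- The first acts on time and applies to every child. Prolonged travel is recorded each month, and "time at risk will be censored for such periods".
- The second is introduced as an addition and acts on events. It censors "malaria cases in children who resided outside their study village for more than half the elapsed study period", judged when the child falls ill.

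The same section gives the effect measure: "Incidence rates will be calculated for each cluster and the ratio of their un-weighted means will give an estimate of the intervention effects".

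The movement data are described under Study procedures and evaluations: "Movement of children will be assessed at monthly intervals on brief questionnaires to estimate the time at risk". Table 1 schedules travel monitoring from June to November in each year. The Design section says that spraying cannot be blinded.

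**The concern.** The first rule is sound: time not spent in the village is not time at risk there, whether or not the child becomes ill. The second rule is different because its test is made when malaria is diagnosed. Take two children, each away for 60% of the elapsed period. If one has malaria on return, that episode is dropped. If the other stays well, the test never arises, and nothing in the text removes that child's 40% resident time. The denominator then holds time in which an event could not have counted.

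This bears on the primary endpoint. The rates in both arms, and the absolute difference between them, would be too low relative to the person-time used. The ratio would also shift if the arms differed in long absence or in how it is reported.

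A second, smaller difficulty is that the threshold has no stated origin. Replacement children join in June 2011, so elapsed time could run from the start of the trial, from the child's own enrolment or from each season. If it runs from June 2010, it spans months in which Table 1 schedules no travel monitoring.

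**Working it through.** **The plan's own figure.** The article gives no mobility figure to reproduce. Its planned person-time does reproduce: 110 children × 2 years × 22/52 × 0.80 = 74.46 child-years per cluster, against 74.4 stated under Sample Size Rationale, a) Clinical. The sample size does not depend on the present point.

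**Inputs.**
- From the article: planning rates, given as "incidence rates of 0.30 (LLINs) to 0.15 cases/child-years (LLINs & IRS").
- Assumed: a share m of children exceeds the half-time limit, with m between 5% and 20%.
- Assumed: such children keep 40% of their time as resident time; all other children keep all of theirs.
- Assumed: the in-village malaria rate is the same in mobile and non-mobile children.

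**Step 1: share of person-time that can yield no counted event.**

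s = 0.4m / [(1 − m) + 0.4m]

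| m | s |
|---|---|
| 5% | 0.02/0.97 = 2.1% |
| 10% | 0.04/0.94 = 4.3% |
| 15% | 0.06/0.91 = 6.6% |
| 20% | 0.08/0.88 = 9.1% |

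These are upper bounds for their inputs. The formula treats all resident time of a flagged child as unable to yield an event, whereas resident time before the child crosses the limit can still do so.

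**Step 2: effect on the rates.** Observed rate = true rate × (1 − s).
- LLIN arm: 0.30 becomes 0.294 (m = 5%) to 0.273 (m = 20%).
- IRS arm: 0.15 becomes 0.147 to 0.136.
- Absolute difference: 0.15 becomes 0.147 to 0.136.

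**Step 3: effect on the ratio.** Observed ratio = true ratio × (1 − s in IRS) / (1 − s in LLIN).
- Equal mobility: the factor is 1, so 0.50 stays 0.50.
- 5% in LLIN, 15% in IRS: 0.934/0.979 = 0.954.
- 10% in LLIN, 20% in IRS: 0.909/0.957 = 0.949.
- 15% in LLIN, 5% in IRS: 1/0.954 = 1.048.

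If the same fraction of the bound s is realised in both arms, the first two factors are the furthest from 1 that those inputs allow.

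**Step 4: check by weekly simulation.** In a 22-week season, 20% of children made one trip of 4 to 16 weeks starting at a random time. Many of them never exceed the half-time limit, so this is a milder scenario than m = 20%.

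| Rule | LLIN rate | IRS rate | Ratio |
|---|---|---|---|
| No exclusion beyond time away | 0.300 | 0.150 | 0.50 |
| Cases dropped, time kept | 0.296 | 0.148 | 0.50 |
| Cases and matching time dropped | 0.300 | 0.150 | 0.50 |

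The matched rule restores the true rates.

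**The case against.** **The time may be removed too.** The article does not say that the mobile children's resident time is kept; this is inferred from silence. The same paragraph uses censoring for time in two other rules, so censoring a case might include that child's follow-up, and the full protocol or SAP may say so. This stands as a caution about certainty. It does not remove the mismatch: even if the case's own time goes, the trigger is still illness, and the equally mobile child without malaria is untouched.

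**The aim is legitimate.** A child living mostly elsewhere may have been infected elsewhere. This stands, and a matched rule serves the same aim.

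**The ratio is robust.** A reader might infer that the primary treatment comparison is biased. The document does not support that. The effect measure is a ratio, and an equal loss in both arms cancels. The article gives no reason to expect long absence to differ by arm, and movement questionnaires are planned for the study children without distinction by arm. What remains is a possibility: the trial is open and absence is reported by questionnaire.

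**Long absence should be uncommon.** At recruitment, "Assurance will also be sought from carers/parents that they expect that the child will remain resident in their village during the transmission season". This limits the size, but it is a statement of expectation, not a bar to travel.

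**A few days away early in the season.** A reader might also infer that very short trips would trigger the rule. The wording concerns residing outside the village, next to a rule on prolonged travel, so that reading is strained.

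**Conclusion.** The point holds as a defect of definition in the primary analysis. A stated rule excludes events by a test that only cases can meet, and no corresponding rule for person-time is given. Followed as written, it understates both arms' incidence rates and their absolute difference. The bound is about 2% to 9% under the assumed 5-20% of children beyond the limit with 40% resident time and equal in-village rates; the simulation suggests less, about 1.5% (0.300 to 0.296).

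It does not show that the rate ratio is biased. With equal long absence and equal reporting, the ratio is unchanged. With 5% against 15%, a true ratio of 1.0 would move to no lower than about 0.95, or to no higher than about 1.05 if the difference ran the other way, provided a similar fraction of the bound is realised in each arm. Every mobility figure here is an assumption.

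**What to change.** Define the residence exclusion by time and apply it to every child regardless of case status: while a child is beyond the threshold, exclude both episodes and person-time, and readmit both when the child falls back within it. State from when elapsed time is counted, for example from the start of each season or from the child's own enrolment. A fixed look-back window is another workable form; the choice matters less than applying it alike to cases and non-cases.

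Add a sensitivity analysis that counts all episodes over resident person-time without the threshold. Report the episodes and person-time excluded by arm, so that readers can see whether absence differed.

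The cost is a small loss of person-time and minor programming. The monthly movement questionnaires already planned supply the data during the scheduled June to November monitoring.

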### Randomisation

An equal number of clusters will be randomized to receive IRS, in addition to the LLINs provided to all enrolled households, and in these all households will be treated. In cluster-randomised controlled trials it is particularly important to minimize imbalance for factors known to be highly correlated with the disease outcome; in this case age and access to health facilities and location. At the village level we will stratify by presence of a primary health care centre (PHC) and geographical location by dividing the total area into four with two of equal area on each bank of the river. Stratification for PHCs will also ensure that the larger villages are evenly distributed in the experimental groups. In addition, balanced randomization will be used to ensure that children of similar ages are enrolled at the village level.

Stratified randomisation of villages to the study groups, as outlined above, will reduce the likelihood of chance imbalances between study arms but as only relatively small number of units can be randomized in such a cluster design, both groups cannot be assumed similar for all factors. Baseline data on spleen rates, parasite prevalence and anaemia will be collected on a representative sample of enrolled children in each village at the beginning of the main transmission season in 2010 to assess imbalances in malaria at village level.

Observer bias will be reduced where feasible. Blood films will be read by microscopists blinded to the identity and intervention status of the subjects. Mosquito collector bias will be reduced by using standard light traps and exit traps, which do not rely on the ability of the fieldworker to collect specimens. Trap catches will be examined by a different person to the trap collector and they will be blinded to the trap location. The processes of the interventions, both for LLINs and IRS, will be closely monitored not only for quality but also to document any bias between the villages.

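### The named test of the primary endpoint leaves out the randomisation strata (PHC presence and area), so it is conservative and gives up most of the precision that stratifying should bring

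*Protocol article*

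**What the plan says.** Three sections of the protocol article bear on this point.

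- **Randomisation.** "At the village level we will stratify by presence of a primary health care centre (PHC) and geographical location", with the study area split into four parts, two on each river bank. The reason given is to limit imbalance in factors strongly related to disease outcome, among them access to health facilities and location. Two PHC levels by four areas make 8 cells (2 x 4; the protocol does not state the number).
- **Sample Size Rationale, a) Clinical.** The calculations give 5-39 clusters per arm. Three reasons support the choice of 35: conservative incidence estimates, conservative drop-out, and that "the value of k may also be reduced by the stratified design, we will recruit 35 clusters in each arm of the trial".
- **Analytical plan, Outcome 1.** "An initial unadjusted analysis will be based on comparisons of the incidence rates between the 2 groups". The effect estimate is the ratio of unweighted cluster means, with an approximate and a bootstrapped confidence interval. The cluster rates will also be used to "perform a hypothesis test based analysis between the 2 groups using a 2 sample unpaired t-test". If its assumptions fail, "a non-parametric test (Mann-Whitney) will be used to compare the 2 groups". In addition, "linear regression can be used to adjust for cluster level covariate effects", and a random-effects Poisson model is planned with year as a fixed effect. For adjustment, "Other potential confounders such as house architecture, bednet use and recent antimalarial treatment will also be adjusted for in the analysis".

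PHC, area and strata appear nowhere in the Outcome 1 analysis.

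**The concern.** Stratifying on factors that predict the outcome balances them between arms. The difference between arm means then varies less from one randomisation to another. An unpaired test does not recognise this: its standard error still contains all the variation between strata. The true sampling error is smaller than the test assumes, so p-values are too large on average and part of the power is lost.

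The design and sample size sections pull one way and the analysis section the other. A lower k is offered as a reason to accept 35 clusters, but the named test works with essentially the full, unreduced k. The Mann-Whitney fallback has the same gap. The regression that could close it is optional and its covariates are not named.

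**Working it through.** **Inputs from the sample size section.** Rates of 0.30 and 0.15 per child-year; 30-60% reduction; k from 0.31 to 0.43; y = 74.4 child-years per cluster (110 x 22/52 x 2 x 0.8 = 74.5). Power and significance level are not stated for the primary endpoint. I assume 80% and two-sided 5%.

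**Step 1: reproduce 5-39.** The unmatched cluster formula for rates is

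c = 1 + (1.96 + 0.84)² x [(λ0 + λ1)/y + k²(λ0² + λ1²)] / (λ0 - λ1)², with (1.96 + 0.84)² = 7.85 from unrounded z-values.

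- Upper end: λ0 = 0.15, λ1 = 0.105, k = 0.43. The bracket is 0.00343 + 0.00620 = 0.00963 and (λ0 - λ1)² = 0.002025, so c = 1 + 7.85 x 0.00963/0.002025 = 38.3, rounded up to 39.
- Lower end: λ0 = 0.30, 60% reduction, k = 0.31 gives 4.8, rounded up to 5.

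The stated range is reproduced. At 90% power it would be 7-51, so 80% fits. The formula has no stratum term, so the 39 takes no credit for stratification. The upper end needs 0.15 as the control rate, although the text attaches that figure to the combined arm.

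**Step 2: power at 35 per arm in that corner, no credit for strata.** Power = Φ[(λ0 - λ1) x √(34/0.00963) - 1.96] = 76%. Reaching 80% needs k of about 0.40: 0.399² = 0.159 against 0.43² = 0.185, or about 14% less between-cluster variance.

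**Step 3: let strata explain a share R² of between-cluster variance.** The protocol gives no value, so R² is an assumption. The true variance term becomes V = 0.00343 + (1 - R²) x 0.00620. The stratified test uses V; the unpaired test still uses 0.00963.

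| R² | V | Power, stratified | Power, unpaired | Type I error, unpaired |
|---|---|---|---|---|
| 20% | 0.00839 | 81.7% | 77.8% | 3.6% |
| 30% | 0.00777 | 84.6% | 78.7% | 2.9% |
| 40% | 0.00715 | 87.4% | 79.6% | 2.3% |

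A t-based interval for the difference would be √(0.00963/0.00839) = 1.07 to √(0.00963/0.00715) = 1.16 times as wide as needed. This does not apply directly to the approximate and bootstrapped intervals that the plan uses for the ratio.

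**Step 4: simulation of the same corner.** 70 clusters in 8 near-equal strata, Poisson counts with log-normal cluster effects, 4,000 runs per setting. R² is here on the log scale.

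| R² | Power, unpaired | Power, stratum terms | Type I error, unpaired | Type I error, stratum terms |
|---|---|---|---|---|
| 0% | 0.78 | 0.77 | 0.050 | 0.050 |
| 20% | 0.80 | 0.82 | 0.034 | 0.048 |
| 40% | 0.81 | 0.87 | 0.022 | 0.044 |
| 60% | 0.82 | 0.93 | 0.016 | 0.048 |

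From R² = 0 to 40%, the unpaired test gains about 3 to 4 points in either calculation. The stratified analysis gains about 10 to 11.

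**Step 5: other planning cases, k = 0.43 and 30% effect, no credit for strata.** A control rate of 0.20 needs 35 clusters. A control rate of 0.30 needs 32, and 35 clusters then give 84% power. At a control rate of 0.15 with k = 0.37, 33 are needed.

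**The case against.** The strongest reply is that nothing here is invalid. The comparison is introduced as an initial unadjusted one and no test is labelled primary. The regression on cluster rates could carry PHC and area, and the covariate list of an adjusted model may properly stand in an analysis plan not shown here. Stratification serves balance whatever test follows. All of this is correct, and it limits the point. What remains is that the article itself names the test, describes it as unpaired, leaves the regression optional, and lists covariates without the stratification factors.

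Three stronger readings are tempting and not supported:

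- *That 35 clusters depend on stratification.* It is the third reason given and is hedged, and no reduced k enters any calculation. A control rate of 0.20 or more justifies 35 without it.
- *That the omission decides whether 80% power is reached.* The shortfall is confined to the corner combining the lowest rate, the smallest effect and the highest k. Even there the simulated unpaired test has power of 0.80-0.82 once strata explain 20-60% of variance; the formula puts it just below 80%.
- *That a switch to Mann-Whitney leaves no rate ratio.* That test replaces only the hypothesis test. The ratio of cluster means and its intervals stay.

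**Conclusion.** The point holds as a loss of efficiency and a mismatch between design and analysis. The named test ignores factors that the plan stratifies on and considers predictive. It is valid but conservative: there is no bias and no excess of false positives.

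In the least favourable planning case, with 20-40% of between-cluster variance explained by strata, power is about 82-87% with stratum terms against about 78-81% without. The unpaired test's true type I error is about 2-4%. These figures rest on the assumed share of variance explained, on 80% power and two-sided 5% as the planning basis, and, in the simulation, on strata of near-equal size. If strata explain nothing, nothing is lost by the unpaired test. Severity: should be fixed.

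**What to change.** Make the cluster-level test a stratified one. Either state that the planned linear regression of cluster rates will include PHC presence and area, in place of the optional wording, or specify a stratified t-test on cluster rates. Add both factors to the random-effects Poisson model. If a non-parametric test is needed, permute arm labels within strata instead of using Mann-Whitney.

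Keep the ratio of cluster means as the effect measure. If log rates are modelled instead, say that the result is a ratio of geometric means and state how clusters with no cases are handled, because this changes what is estimated.

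The cost is wording and a few degrees of freedom. An unpaired test on 70 clusters has 70 - 2 = 68. Main effects of PHC and area use 1 + 3 = 4 of them; all 8 cells use 7. If strata explain nothing, the simulated loss is about one point of power (0.78 to 0.77).
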